**Methods/design:**

This study is a multi-center, randomized, assessor-blinded trial with an active control conducted in conjunction with a cost-effectiveness analysis and qualitative research. Participants with non-acute low back pain with or without leg pain after back surgery who have a Visual Analogue Scale (VAS) pain intensity score ≥ 50 mm will be randomly assigned to either the EA with UC group (n = 54) or the UC group (n = 54). Following randomization, participants in both groups will receive the same UC treatment twice a week for a four-week treatment period. Participants assigned to the EA with UC group will additionally receive EA twice a week for the same four-week period. The primary outcome measure will be assessed using a VAS pain intensity score for low back pain. The secondary outcomes will include the Oswestry Disability Index, EuroQol 5-Dimension score, and drug intake. The primary and secondary outcomes will be measured at one, four, and eight weeks post randomization.

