### Design

This study is a multi-center, randomized, assessor-blinded trial with two parallel arms and an active control. This study will be conducted in three hospitals in South Korea. Participants will be independently recruited at each hospital site through online advertisements placed on the hospital website and offline on-site advertisements, such as hospital bulletin boards, to obtain the appropriate participant enrollment and target sample size. Potential participants will be required to undergo screening to determine their eligibility. When eligible, participants will be asked to provide written informed consent, after which the baseline evaluation will be conducted by a study researcher. At screening, a clinical research coordinator (CRC) will collect information on various basic sociodemographic characteristics such as gender, age, vital signs, height, weight, and medication history. Korean medicine doctors (KMDs) will collect information on the medical history of individuals who have received spinal surgery, such as the timing of surgery, type of surgery (i.e. fusion, decompression, or discectomy), surgically involved vertebra(e), number of surgeries, time of pain, onset of symptoms, and duration of symptoms. On their second visit, screened participants who are considered eligible for trial participation based on the inclusion and exclusion criteria will be randomly allocated using a 1:1 ratio to either the EA plus UC group or the UC alone group. After randomization, the treatment procedure will be scheduled and managed by a CRC. To maximize participant retention, there will be flexibility during the visit period and researchers will allow actual visits to be within seven days of prescheduled visits. The post-treatment follow-up will occur one, four, and eight weeks following the four-week interventional period to know whether the treatments effects are maintained.

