### Interventions

#### EA with UC group

In the EA with UC group, both acupuncture and EA will be performed. The intervention will be administered by KMDs using 0.25-mm diameter × 40-mm length disposable stainless steel needles (Dongbang Acupuncture Inc., South Korea) and will be provided a total of eight sessions (two sessions/week) for a period of four weeks. Semi-standardized acupuncture points will be used. In other words, Jia-ji (six acupoints, bilateral Ex-B2 at L3, L4, and L5) will be used as the required and standardized points; a maximum of nine acupuncture points will be used as additional points. These additional points will be selected depending on the patients’ symptoms. Electrical stimulation will be applied to four acupuncture points of Jia-ji (bilateral Ex-B2 at L3 and L5) and performed for 15 min with a biphasic waveform current, which utilizes alternating interrupted waves and continuous waves at 50 Hz in a triangular form and a compressional wave [33] using an electronic stimulator (Fig. 3, ES-160, ITO Co. Ltd., Tokyo, Japan). The procedure for EA treatment will be designed to reflect actual clinical settings and will be based on consensus among 21 acupuncture and spinal disorder experts in several offline meetings to ensure the feasibility of the study design.

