### Outcome measurements

#### Primary outcome

The primary outcome of this study is the pain intensity of LBP after back surgery as assessed by a VAS. Post-surgical LBP severity will be quantified using a VAS pain intensity score as determined on a 100-mm horizontal line, where 0 indicates no pain and 100 indicates intolerable pain [35, 36]. The level of back pain during the previous week will be assessed using a 100-mm pain VAS at baseline (visit 2), before each treatment session (visits 2–9), and at each post-treatment follow-up visit (visits 10–12); the primary endpoint will be VAS pain intensity score at visit 10, representing treatment completion. The outcome measures will be assessed before treatment at each visit to ascertain the effectiveness of the previous treatment(s).

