### Sample size

An appropriately powered full-scale sample size has been estimated using the mean between-group difference in the primary endpoint (VAS pain intensity score for LBP) identified in the previous pilot study. Based on intention-to-treat (ITT) analysis, the mean difference and standard deviation (SD) in the VAS pain intensity score for LBP between the EA plus UC group and UC alone group is estimated to be 14.02 mm ± 22.12 mm. Although this reduction in pain intensity is not moderately clinically meaningful, it does represent a minimally important difference [41].

The total number of individuals required per group is 40, considering a two-tailed test with 80% test power and a 5% significance level. After accounting for a 25% drop-out rate and the 1:1 allocation ratio, the final sample size per group has been calculated to be 54, resulting in a total sample size estimate of 108 for a full power analysis.

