### Statistical analysis

The statistical analysis will be conducted using both the ITT and per-protocol (PP) analysis principles in parallel. Multiple imputation methods will be used for missing data in the ITT analysis. A PP analysis will be performed as a secondary analysis excluding data from drop-outs for any reason. An interim analysis will not be performed. An independent t-test or Wilcoxon rank sum test will be used to analyze continuous data to test for significance in between-group differences and will be presented as the mean ± SD. Chi-square test or Fisher’s exact test will be conducted for categorical data and the data will be described as the frequency and percentage (%). To analyze the VAS pain intensity score as the primary outcome, we will perform an analysis of covariance (ANCOVA) considering the baseline scores as covariates and treatment group as the fixed factor. A paired t-test or Wilcoxon signed rank test will be performed to analyze within-group differences pre and post treatment. Repeated measure analysis of variance (RMANOVA) will be used to analyze the between-group differences at each visit. Subgroup analysis will be conducted according to age, gender, and medical history (e.g. the existence of osteoporosis, pre-surgery diagnoses), which may have the possibility of affecting the treatment effects on each outcome.

A safety assessment will be performed for all AEs occurring during the study period. The incidence of AEs, AEs leading to withdrawal, and SAEs will be summarized by group and analyzed using Fisher’s exact test or chi-square test.

All statistical analyses will be conducted by a designated statistician blinded to group allocation with SAS® Version 9.4 (SAS institute Inc., Cary, NC, USA) for Windows. The level of significance will be set at 5%.

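### Repeated-measures ANOVA is named for the group difference at each visit, but its standard tests give a visit average and a global interaction, so whether the effect is maintained is not directly answered

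*Protocol article*

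**What the plan says.** The Statistical analysis section makes a baseline-adjusted ANCOVA the analysis of the primary outcome, and the Primary outcome section sets the primary endpoint at visit 10. For the course over time, the section adds that "Repeated measure analysis of variance (RMANOVA) will be used to analyze the between-group differences at each visit". It states no group-by-visit term, visit contrast, covariance structure or sphericity correction. Multiple imputation is planned for the ITT analysis, and the per-protocol analysis leaves out drop-outs.

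The Primary outcome section sets the measurements: "The level of back pain during the previous week will be assessed using a 100-mm pain VAS", with scores taken "before each treatment session (visits 2–9), and at each post-treatment follow-up visit (visits 10–12". Treatment is given as "a total of eight sessions (two sessions/week) for a period of four weeks". The Design section says "The post-treatment follow-up will occur one, four, and eight weeks following the four-week interventional period" and gives the purpose, which is to learn whether effects persist. The abstract times the same assessments differently: "The primary and secondary outcomes will be measured at one, four, and eight weeks post randomization".

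**The concern.** The sentence pairs a method with a question that the method's standard output does not answer. It is the only method in the section that uses the repeated scores jointly. A report that follows it literally would present F tests for group, visit and group-by-visit. A significant interaction says that the group difference is not constant. It does not say whether the difference is present at visit 11 or 12, or how large it is. An effect that fades after treatment and one that appears late and persists can produce the same significant interaction.

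The interaction test also relies on sphericity, meaning equal variances of the differences between all pairs of visits. Closely spaced scores with overlapping recall, followed by scores weeks apart, make that unlikely. At stake is how the secondary durability result is read, not the primary conclusion.

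**Working it through.** **The plan's own figure.** The Sample size section gives a difference of 14.02 mm, SD 22.12 mm, two-sided 5% and 80% power. n = 2 × (1.960 + 0.842)² × 22.12² / 14.02² = 39.1, so 40 per group. Allowing for 25% drop-out, 40 / 0.75 = 53.3, so 54 per group and 108 in total. The stated figures reproduce, and they rest on the visit-10 comparison, not on the repeated-measures analysis.

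**What each test addresses.** Let d_j be the true group difference at visit j.
- Group main effect: the mean of the d_j over the visits is zero.
- Group-by-visit: all d_j are equal.
- Maintenance: the sizes of d_11 and d_12.

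Neither of the first two is a statement about d_11 or d_12. Contrasts for single visits can be drawn from a repeated-measures model, but they are a further step that the text does not name.

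**Spacing.** Visits 2 to 12 give 11 scores, of which 10 are post-baseline. Eight sessions at two a week are about 3.5 days apart. With a 7-day recall, neighbouring treatment-period scores share (7 − 3.5) / 7 = one half of their window. On the same spacing, about half of the visit-3 window lies before visit 2, when randomization takes place. On the Design section's timing, visits 10, 11 and 12 fall at about weeks 5, 8 and 12, so visits 11 and 12 are four weeks apart. The abstract's timing from randomization conflicts with this, and the two must be reconciled before the spacing is fixed.

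**Sphericity.** The article gives no correlations, so these are assumed. Times: weeks 0, 0.5, 1, 1.5, 2, 2.5, 3, 3.5, 5, 8 and 12. Correlation: r^(weeks apart), with r from 0.50 to 0.95. With k = 11, S the correlation matrix, C = I − J/k (J all ones) and A = CSC, the Greenhouse-Geisser epsilon is tr(A)² / [(k − 1) tr(A²)]. A value of 1 means sphericity.

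The table shows null rejection rates at nominal 5% from 4,000 simulated trials per row, with 54 per group and complete data. The uncorrected interaction test has 10 and 10 × 106 = 1,060 degrees of freedom.

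| r per week | epsilon | group-by-visit, uncorrected | group-by-visit, Greenhouse-Geisser | group main effect |
|---|---|---|---|---|
| 0.50 | 0.63 | 8.9% | 5.0% | 4.6% |
| 0.70 | 0.49 | 10.7% | 5.2% | 4.6% |
| 0.80 | 0.41 | 11.0% | 5.4% | 4.5% |
| 0.90 | 0.33 | 12.5% | 5.5% | 4.8% |
| 0.95 | 0.29 | 13.3% | 5.1% | 4.8% |

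A second simulation let the correlation decay per visit instead of per week (2,500 trials per setting). At 0.5, 0.7, 0.85 and 0.95 the uncorrected test rejected in 8.4%, 9.6%, 12.6% and 13.0%. Both structures therefore give about 8% to 13%. The inflation is confined to the uncorrected interaction test.

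**The case against.** The strongest reply is that this is one loosely worded sentence about a secondary analysis in a condensed article. Visit contrasts, covariance structure and sphericity correction are details that such an article leaves to the full protocol or SAP, and the text never says that the F test will be uncorrected. The section also lists t-tests or Wilcoxon tests for continuous data, which could be applied at visits 11 and 12. Much of this stands. The missing correction is not in itself an error. What remains is that the article does name a method for a question, and the two do not match. A correction repairs only the interaction test.

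A reader might infer several stronger things that the documents do not support:
- **That the assumptions fail.** No correlation is given, so sphericity is implausible rather than shown to be violated. Unequal spacing alone breaks nothing when visit is a factor, and the group main effect keeps its level.
- **That drop-out defeats the method.** The phrase "After accounting for a 25% drop-out rate" refers to a planning allowance, and multiple imputation covers missing scores in the ITT set. Only unimputed data would shrink to 108 × 0.75 = 81 complete cases. The per-protocol set excludes drop-outs under any model.
- **That ten per-visit tests inflate the any-visit error.** Simulated rates were 15% to 36%, but that assumes separate tests at every visit, a different reading of the sentence from the one criticized here. The primary endpoint is fixed at visit 10 in any case.
- **That the effect would be diluted to about 8.3 mm.** This is the 11-visit mean of an assumed linear rise to 14.02 mm at visit 10, held thereafter: (9 × 7.01 + 2 × 14.02) / 11 = 8.28. The plan states neither that ramp nor a visit-averaged target.

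**Conclusion.** The point holds for the secondary longitudinal analysis. The named method does not, by its standard tests, give the group difference at each visit, so persistence of effect at visits 11 and 12 is not directly answered. This conclusion needs no assumption about the data.

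The second part is conditional. If the group-by-visit test were run uncorrected, and if correlations decay over time in the assumed range of 0.50 to 0.95, its null rejection rate would be about 8% to 13%. With a Greenhouse-Geisser correction it is 5.0% to 5.5%. The visit-10 ANCOVA and the sample size (40 evaluable and 54 randomized per group, 108 in total) are unaffected.

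**What to change.** Replace the repeated-measures ANOVA sentence with a mixed model for repeated measures on post-baseline VAS:
- Terms: treatment, visit, treatment-by-visit, baseline VAS, baseline-by-visit and center.
- Covariance: unstructured, with a stated fallback if the model does not converge, and Kenward-Roger degrees of freedom.
- Reporting: the treatment difference with 95% CI at each visit, in particular visits 11 and 12, labelled as supportive to the visit-10 ANCOVA.

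This gives baseline-adjusted visit differences directly, uses participants with incomplete scores and does not require sphericity. Restricting the model to fewer visits is optional and serves convergence only: ten post-baseline visits need 10 × 11 / 2 = 55 covariance parameters, six need 6 × 7 / 2 = 21. The abstract and the Design section should also be reconciled on when the follow-up visits fall.

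The cost is analysis wording. SAS 9.4, already named in the article, fits this model. The small downside is the need to specify the fallback covariance structure in advance. The primary analysis and the sample size do not change.

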### Cost-effectiveness analysis

The economic evaluation study will be conducted along with the comparative effectiveness RCT. We aim to estimate the short-term cost-effectiveness of EA with UC compared to UC alone from the South Korean societal perspective. Cost components of both treatments will be defined and measured according to the identification, measurement, and valuation process. Cost data from all individual participants will be obtained using separately developed economic case report forms. Effectiveness and utility measurements will be collected from the main comparative effectiveness RCT. Quality of life will be measured by the EQ-5D instrument; quality-adjusted life years (QALYs) gained in both groups will be calculated using the area under the curve method. Cost and effectiveness (utility) will be analyzed as intention to treat and missing data will be imputed using multiple imputations. In the deterministic analysis, mean values of cost and effectiveness (utility), derived from generalized linear model adjusting for potential confounders, will be used as a representative value for calculating ICER (incremental cost-effectiveness ratio). We will use the bootstrapping percentile method to identify the sampling uncertainty of ICER. Cost-effective planes and cost-effectiveness acceptability curves will also be estimated to display and interpret statistical uncertainty and economic decision-making according to the maximum willingness to pay. If we could not observe the fully yield cost and effective outcomes of both alternatives in this short-term within trial evaluation, we will develop a decision analytic model and conduct a longer-term period evaluation.

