#### Secondary outcome

Regarding secondary outcomes, the Oswestry Disability Index (ODI) will be used to assess disability associated with back pain [37] and the EuroQol 5-Dimension (EQ-5D) scale [38] will be employed for health-related quality of life.

The ODI consists of ten questions pertaining to daily activities and covers the following: experiencing general pain, practicing self-care (e.g. washing, dressing), lifting objects, sitting, standing, walking, sleeping, travelling, engaging in sexual activity if applicable, and participating in social activities. The items are rated on 6-point scales scored in the range of 0–5, with higher scores indicating higher pain-associated disability. The participants will be asked to complete the validated Korean version [39] of the ODI before treatment on the second and sixth visits and at each post-treatment follow-up (visits 10–12).

The validated Korean version of the EQ-5D [40] will be used to assess health-related quality of life in post-surgical LBP patients. The EQ-5D consists of five dimensions: usual activities; mobility; pain/discomfort; anxiety/depression; and self-care. The scales for these dimensions are in the range of 1–3 and lower scores represent a better health status. The EQ-5D scores will be evaluated before treatment at the initial treatment session (second visit) and at each follow-up (visits 10–13). For cost-effectiveness analysis, EQ-5D will be additionally evaluated via telephone at the 13th visit.

Changes in medicine intake and dosage will be investigated through interviews at each visit. Additional pain-related treatments will be allowed and the type and frequency will be recorded as part of the feasibility design (e.g. physiotherapy, medication).

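### The percentile bootstrap interval for the ICER is specified without a condition, and it cannot be interpreted if more than about 2.5% of replicates have a QALY difference at or below zero

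*Protocol article*

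**What the plan says.** The Cost-effectiveness analysis section of the protocol article sets the aim: "We aim to estimate the short-term cost-effectiveness of EA with UC compared to UC alone". The denominator of the ratio comes from EQ-5D: "quality-adjusted life years (QALYs) gained in both groups will be calculated using the area under the curve method". For uncertainty it names one method for the ratio itself: "We will use the bootstrapping percentile method to identify the sampling uncertainty of ICER". The next sentence adds graphical summaries: "Cost-effective planes and cost-effectiveness acceptability curves will also be estimated to display and interpret statistical uncertainty". Mean cost and effect are to come from a generalised linear model with confounder adjustment, by intention to treat, with multiple imputation.

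The section does not say what happens to replicates in which the QALY difference is zero or negative, and it does not mention net benefit. The article gives no expected QALY difference, utility SD or cost. The Sample size section rests on the pain VAS alone: "the final sample size per group has been calculated to be 54, resulting in a total sample size estimate of 108".

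**The concern.** The ICER is the cost difference divided by the QALY difference, so it is discontinuous where the QALY difference is zero. Its sign does not identify the conclusion. A negative ratio arises when electroacupuncture is cheaper and better (dominant) and also when it is dearer and worse (dominated). A positive ratio arises when it is dearer and better and also when it is cheaper and worse. Sorting the replicates by size and reading off the 2.5th and 97.5th percentiles is sound only while the QALY difference stays on one side of zero.

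Once more than about 2.5% of replicates cross, they can fill a whole tail. If most of them are dearer and worse, they appear at the bottom of the ranking. A reader would then take a negative lower limit as possible cost saving when it means the opposite. Cost-effectiveness is part of the stated hypothesis and objective, so this interval is likely to be quoted.

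**Working it through.** **Inputs from the protocol article (Sample size).** VAS difference 14.02 mm, SD 22.12 mm, two-sided 5%, 80% power, 25% drop-out, 40 per arm before drop-out and 54 after.

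**The plan's own figure.** n = 2 × [22.12 × (1.960 + 0.842) / 14.02]² = 39.08, so 40 per arm. 40 / 0.75 = 53.3, so 54 per arm and 108 in total. The stated size reproduces. It was chosen for the VAS, with standardised effect 14.02 / 22.12 = 0.634.

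**Assumed, because the documents give nothing.** Let d be the standardised QALY difference, taken from 0.2 to 0.634, and n the effective number per arm. Since missing data are imputed, n lies between about 40 and 54. With the normal approximation, the observed QALY difference divided by its standard error has mean z = d × √(n/2).

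- Share of replicates with a negative QALY difference, when the observed effect equals the expected one: Φ(−z).
- Chance that more than 2.5% of replicates are negative: Φ(1.96 − z).

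Example: d = 0.2 and n = 54 give z = 0.2 × √27 = 1.04, so Φ(−1.04) = 15% and Φ(0.92) = 82%.

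| d | Share negative, n = 40 | Share negative, n = 54 | Chance share exceeds 2.5%, n = 40 | Chance share exceeds 2.5%, n = 54 |
|---|---|---|---|---|
| 0.2 | 19% | 15% | 86% | 82% |
| 0.3 | 9% | 6% | 73% | 66% |
| 0.4 | 3.7% | 1.9% | 57% | 45% |
| 0.5 | 1.3% | 0.5% | 39% | 26% |
| 0.634 | 0.2% | 0.05% | 19% | 9% |

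**What the interval looks like.** These are 20,000 bootstrap replicates with 54 per arm over 12 weeks, with an assumed cost difference of 200 and cost SD of 300 in arbitrary units.

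- Utility gain 0.03, SD 0.15 (d = 0.2). The ICER is 200 / (0.03 × 12/52) = 28,889. The percentile interval runs from about −270,000 to 306,000. About 15% of replicates are dearer and worse and almost none are cheaper and better, so the negative limit consists of dominated replicates. The Fieller set is unbounded, which is the honest answer here.
- Utility gain 0.05, SD 0.10 (d = 0.5). The percentile interval is 5,935 to 68,829 and Fieller gives 6,402 to 74,055. With 0.4% of replicates negative, the percentile interval is usable.

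**Does the time horizon matter?** With d held fixed, no. It multiplies the QALY mean and SD by the same factor, which cancels in z. At d = 0.2 and n = 54 the simulated share was 15% at both 12 and 52 weeks.

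**Does adjustment matter?** Yes. Assume EQ-5D at weeks 0, 5, 8 and 12, equal correlation of 0.4 to 0.7 between visits, and baseline utility as a covariate. The trapezoid weights are 2.5/12, 4/12, 3.5/12 and 2/12, with sum of squares S = 0.267. The unadjusted variance factor is V = S + r(1 − S), the covariance with baseline is C = 0.208 + 0.792r, and the adjusted SD factor is √(V − C²). This is 0.53 at r = 0.4 and 0.45 at r = 0.7. For a utility gain of 0.04 with SD 0.15, r = 0.5 and about 0.8 of the gain reaching the area under the curve, the factor is 0.52. Then d = 0.04 × 0.8 / (0.15 × 0.518) = 0.41. The expected negative share is 1.6%, against 13% if the QALY SD is taken as the full single-visit SD without adjustment. The chance of exceeding 2.5% is still Φ(1.96 − 0.41 × √27) = 43%.

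**The case against.** The strongest reply is that the section already plans the cost-effectiveness plane and the acceptability curve. Both stay valid when the QALY difference changes sign, and the plane would show a reader how the replicates are spread. That stands, and it confines the problem to one reported statistic. It does not correct that statistic, and nothing in the section says when to withhold it.

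A second reply is that a condensed article may leave the handling of quadrants to the analysis plan. That would answer a complaint about missing detail. Here, however, the article positively names a method for the ratio and attaches no condition to it.

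A reader might also infer three stronger things that the documents do not support:

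- **That a sign change is likely in this trial.** The article gives no QALY effect. The chance is high at d of 0.3 or below, about even at 0.4, and small if QALYs move as the VAS does. Adjustment for baseline utility lowers it further.
- **That the short follow-up causes the problem.** At a fixed d the horizon cancels. Nor is it fixed at 12 weeks. The Design section has "The post-treatment follow-up will occur one, four, and eight weeks following the four-week interventional period", whereas the abstract has "The primary and secondary outcomes will be measured at one, four, and eight weeks post randomization". The Secondary outcome section adds "For cost-effectiveness analysis, EQ-5D will be additionally evaluated via telephone at the 13th visit" and gives no week for that visit in the text shown.
- **That a percentile interval for an ICER is always meaningless.** At d = 0.5 it was close to Fieller.

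**Conclusion.** The point holds as a conditional one. An unconditional percentile interval for the ICER is unsafe in a trial sized only for pain. The 2.5% threshold is the practical marker, because beyond it one nominal limit can consist of replicates from the wrong side of zero. At 54 per arm the chance of passing it is about 82%, 45% and 9% for d of 0.2, 0.4 and 0.634, and at 40 per arm about 86%, 57% and 19%. These figures rest on an assumed QALY effect, a normal approximation and no gain in precision from covariates; such a gain acts like a larger d. The consequence is a possibly misleading interval in a secondary economic analysis, with the plane, the acceptability curve, the primary endpoint and the sample size unaffected.

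**What to change.** Amend the economic analysis wording before the data are analysed:

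1. From the same bootstrap replicates, report incremental cost and incremental QALY, each with a 95% interval.
2. Report incremental net monetary benefit (willingness to pay × QALY difference − cost difference) with a 95% interval at willingness-to-pay values named in advance. This is linear in both differences and has no discontinuity at zero.
3. Keep the planned plane and acceptability curve, and state the share of replicates in each quadrant.
4. Give a percentile interval for the ICER only if essentially all replicates have a QALY difference on the same side of zero, that is, in one quadrant or in two adjacent quadrants with a clear ordering. Otherwise state that no interval is given, and why.

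The cost is a little extra reporting and, in some outcomes, no ICER interval. No new data or computation beyond the planned bootstrap is needed.
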